## Results

The clinical trial registration was approved in May 2022. Recruitment and data collection for the trial are ongoing, and the results of this study are expected to be completed by the end of December 2026.

## Discussion

### Potential Relevance and Impact of the Study

This randomized clinical trial, with 2 parallel arms and blinded evaluation, compares the effects of AT and BI on clinical control in individuals with moderate to severe asthma. The effects of physical exercise on people with asthma have been widely discussed in recent years [14], and physical exercise has been proposed as a nondrug therapy for asthma management. AT promotes anti-inflammatory effects in patients with asthma and improves exercise-induced bronchoconstriction [12]. In addition, physical training improves physical conditioning and health-related quality of life, and reduces bronchial hyperresponsiveness, the use of long-term bronchodilators and corticosteroids, and asthma symptoms [5,7,14,27,58,59]. BI, aimed at increasing PADL in people with asthma, also promotes better disease control [8]. Furthermore, recent studies have shown that a higher number of steps per day is associated with better clinical control of moderate to severe asthma [60], and that the minimum clinically significant difference is 1413 steps per day [61]. The results of this study may be highly relevant to clinical practice, as they will enable a similar understanding of how both interventions can improve clinical control of asthma in the short and medium term, regardless of the approach used.

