**Objectives**

As previously mentioned, evidence suggests that AT or BI can improve asthma symptoms and reduce comorbidities. However, the comparison between these interventions in improving asthma control remains poorly understood. We hypothesize that these interventions will promote similar benefits in asthma control and quality of life in people with asthma. The main objective of this study is to compare the effects of AT versus BI in increasing physical activity for clinical asthma control. The secondary outcomes will include quality of life, physical activity level, sleep quality, asthma exacerbations, behavioral stages of physical activity, body composition, anthropometric variables, anxiety and depression symptoms, and cardiopulmonary exercise testing (CPET).

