## Methods

### Study Design

This study is a randomized trial with 2 parallel arms and a blinded evaluation. The study will be conducted at a university hospital that offers specialized treatment for moderate to severe asthma. The study protocol was developed in accordance with the SPIRIT (Standard Protocol Items: Recommendations for Interventional Trials) checklist guidelines [15], and the trial is registered at ClinicalTrials.gov (NCT05364632). The study flow diagram is presented in Figure 1.

After a regular medical visit, adult outpatients with asthma will be invited to participate in the study, and asthma pharmacotherapy will be maintained during the intervention. Initially, eligible patients will be randomized by a researcher not involved in the study using a computer-generated sequence into 2 groups: the AT group or the BI group. The total duration of each intervention for both groups will be 12 hours (720 minutes). Both groups will be evaluated before and after the interventions and again 16 weeks later. The evaluations will be carried out in a blinded fashion by an evaluator who will not be directly involved in the interventions.

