### Participants

The study will include adults of both sexes aged 18 to 65 years with moderate to severe asthma [16] who are physically inactive (less than 150 minutes of moderate to vigorous physical activity per week) [17], and patients with uncontrolled asthma (Asthma Control Questionnaire [ACQ]≥1.5) [18]. In addition, the following inclusion criteria will be considered: diagnosis of asthma based on Global Initiative for Asthma recommendations [1], outpatient medical treatment for at least 6 months, and a stable clinical status for at least 30 days (no hospitalizations, visits to emergency services, or medication changes) [19].

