### Interventions

#### Asthma Education Program for Both Groups

All people in both groups will participate in a brief asthma education program of 90 minutes. The educational program will be conducted in a class through group discussions and video presentations. Educational topics will include asthma pathophysiology, medication and peak flowmeter use, self-monitoring of symptoms, environmental hygiene [1,26], and physical activity recommendations and benefits [17].

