### Participant Timeline

The schedule of enrollment, allocations, interventions, and assessments is outlined in Table 2. The recruitment of the study participants began in August 2022.

**Table 2 table2:** Schedule of enrollment, interventions, and assessments.

Study period			Enrollment (t1)		Allocation (0)		Baseline		After allocation (8 wk)		Follow-up (16 wk)

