**Assessments**											
	Lung function					✓					
	PADL^a^ and sedentary behavior	✓						✓		✓	
	Asthma clinical control	✓						✓		✓	
	Asthma exacerbation					✓		✓		✓	
	Quality of life					✓		✓		✓	
	Anxiety and depression symptoms					✓		✓		✓	
	Barriers to performing PADL					✓		✓		✓	
	Behavioral stage for PADL					✓		✓		✓	
	Anthropometric data					✓		✓		✓	
	Body composition					✓		✓		✓	
	Sleep quality					✓		✓		✓	
	CPET^b^					✓		✓		✓	

^a^PADL: physical activity in daily life.

^b^CPET: cardiopulmonary exercise testing.

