### Conclusions

To the best of our knowledge, this will be the first study to compare the effects of AT versus BI on increasing physical activity for clinical asthma control. Therefore, the results obtained in the proposed protocol may provide essential information for health care professionals when recommending these approaches to people with asthma. Additionally, this study may help clarify whether the potential short-term gains following the intervention are maintained in the medium term in people with moderate to severe asthma.

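### The statement that the trial will show how both interventions improve asthma control rests on change over time, which selection on a high ACQ and shared education can produce alone; the randomised AT-versus-BI contrast is unaffected

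*Protocol article*

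**What the plan says.** - **Selection.** The Participants section admits "patients with uncontrolled asthma (Asthma Control Questionnaire [ACQ]≥1.5". The ACQ is also the primary outcome. The second entry measure is physical inactivity, defined as under 150 minutes of moderate to vigorous activity per week.
- **Schedule.** In Table 2 ("Schedule of enrollment, interventions, and assessments") the row "Asthma clinical control" is ticked at Enrollment, at 8 weeks and at follow-up, not under Baseline. Physical activity in daily life follows the same pattern. Quality of life, anxiety and depression, sleep, body composition and CPET are all ticked under Baseline.
- **Arms.** Study Design randomises patients "into 2 groups: the AT group or the BI group". There is no untreated or education-only arm.
- **Shared co-intervention.** "All people in both groups will participate in a brief asthma education program of 90 minutes". Its content includes medication use and self-monitoring of symptoms. Its timing relative to the ACQ is not given.
- **Expected result.** Objectives: "We hypothesize that these interventions will promote similar benefits in asthma control and quality of life in people with asthma".
- **Analysis.** Statistical Analysis Planning names a two-way repeated measures ANOVA for time and group interactions.
- **Intended reading.** The Discussion says "they will enable a similar understanding of how both interventions can improve clinical control of asthma in the short and medium term", and adds that this holds whichever approach is used. The Conclusions say "this study may help clarify whether the potential short-term gains following the intervention are maintained in the medium term".

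**The concern.** Asthma control varies from one reading to the next. A group chosen because one reading was at or above a cut will, on average, score lower on the next reading without any treatment. If the qualifying score is also the starting point for change, that fall is counted as improvement. Any effect of the education session, if it follows the qualifying ACQ, and any other effect of time are added to it.

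The authors expect similar change in both arms. The likely picture is thus no clear group difference together with a significant time effect, and that is the picture these artefacts would give with two ineffective interventions. Later readings are not truncated, so the apparent fall does not rebound at follow-up and looks like a gain that lasted. What is at stake is whether the trial may say that either intervention improves control, as distinct from how the two compare.

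**Working it through.** **1. The plan's own figure.** With a difference of 0.5, SD 0.6, two-sided 5% and 80% power, the two-sample t calculation gives 23.6, so 24 per arm (power 0.807 at 24), as stated. Adding 15%, 48 × 1.15 = 55.2, gives the stated 56. A one-arm paired calculation with the same inputs would need only 14. The trial was therefore sized for the between-arm difference.

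**2. Inputs for the artefact.** From the article: cut c = 1.5; 24 per arm, 48 in total; clinically significant change 0.5. Assumed, because the article does not give them: clinic ACQ roughly normal with SD σ = 1.0, clinic mean μ = 1.0, 1.5 or 2.0, test-retest correlation ρ = 0.7, 0.8 or 0.9, and no treatment or education effect.

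**3. Formulas.** Let a = (c − μ)/σ and λ = φ(a)/(1 − Φ(a)).
- Expected fall = σ(1 − ρ)λ.
- Variance of the qualifying score among those selected: V = σ²(1 + aλ − λ²).
- SD of the change = √[(1 − ρ)²V + σ²(1 − ρ²)].
- Rejection rate: noncentral t with noncentrality (fall / SD of change) × √n.

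**4. Worked case, μ = 1.5, ρ = 0.8.** a = 0 and λ = 0.798. Fall = 0.2 × 0.798 = 0.16. V = 1 − 0.798² = 0.363. SD of change = √(0.04 × 0.363 + 0.36) = 0.61. With n = 48 the noncentrality is 0.16/0.61 × √48 ≈ 1.8, and the test rejects in about 43% of trials. With n = 24 it rejects in about 23%.

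**5. Range** (null fall in ACQ points; share of trials in which a two-sided 5% paired test on 48 patients rejects):

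| Clinic mean | ρ = 0.9 | ρ = 0.8 | ρ = 0.7 |
|---|---|---|---|
| 1.0 | 0.11; 42% | 0.23; 72% | 0.34; 89% |
| 1.5 | 0.08; 23% | 0.16; 43% | 0.24; 60% |
| 2.0 | 0.05; 12% | 0.10; 20% | 0.15; 29% |

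The fall is 10% to 68% of the 0.5-point threshold (0.05/0.5 to 0.34/0.5). The paired test stands in for the time effect of the ANOVA.

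**6. Persistence and the randomised contrast.** A null simulation with μ = 1.5, σ = 0.8 and ρ = 0.8 gives a mean of 2.14 at the qualifying reading, 2.01 at 8 weeks and 2.01 at follow-up. A separate pre-treatment reading not used for selection also averages 2.01, so the fall measured from it is zero. The between-arm difference in change is 0.00.

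**The case against.** The strongest reply is that the trial is comparative throughout. The objective, the sample size and the group-by-time analysis all concern AT against BI, and randomisation protects that contrast. An active comparator without an untreated arm is a legitimate design for that question. This stands. A reader might infer that the primary comparison is biased; it is not, because the artefact is expected equally in both arms.

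A reader might also infer that the article asserts lasting gains. It does not: Strengths and Limitations and the Conclusions pose maintenance as a question, in conditional terms. The sentence on how both interventions can improve control is hedged too, but it still describes an effect of each intervention, which the comparison of two active arms cannot show.

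Nor do the documents establish that no second ACQ was taken. The Abstract lists the ACQ among assessments made before and after the intervention, Statistical Analysis Planning refers to clinical and physical activity data obtained at baseline, and Table 2 is not a strict chronology (its Baseline column follows Allocation, while Randomization places allocation after the initial assessments). The supportable statement is that Table 2 schedules no pre-treatment ACQ other than the enrollment value.

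The size is assumption. Thirty days of clinical stability, at least 6 months of outpatient treatment, optimised medication and a specialist clinic may all reduce the artefact or place the clinic mean above the cut, where it is smallest. It is also tempting to say that 17% to 36% of patients (clinic mean 1.5, correlation 0.9 to 0.7) would show a false gain of 0.5 or more. Most of that is test-retest noise: without selection the figure is 13% to 26%, and the article plans no responder analysis.

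**Conclusion.** The point holds for the reading of change over time, and only there. Selection on the primary outcome, an enrollment value as the only scheduled pre-treatment ACQ, two active arms and shared education mean that a fall in both arms cannot be attributed to either intervention. Under the stated assumptions (SD 1.0, clinic mean 1.0 to 2.0, correlation 0.7 to 0.9) the null fall is 0.05 to 0.34 points, with rejection in about 12% to 89% of trials against a nominal 5%. Even the mildest case more than doubles the nominal rate, but the documents do not show where in the range this clinic lies. An education effect would add to the fall if the session comes after the qualifying ACQ, which is not stated. Physical activity has the same structure, but no size can be put on it. The listed limitations (subjective questionnaires, a single centre) do not cover any of this.

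**What to change.** 1. In the analysis plan and in the Discussion (Potential Relevance, Strengths and Limitations, Conclusions), limit efficacy conclusions on ACQ and physical activity to the AT-versus-BI contrasts at week 8 and at follow-up, with confidence intervals.
2. State that the time effect and the within-arm changes are descriptive and will not support a claim that either intervention improves control. Give the reason: selection on the outcome and no untreated arm.
3. Report the change from week 8 to follow-up as description and as a between-arm difference, not as proof that a treatment gain was maintained. In the null simulation that change is zero (2.01 to 2.01), so a pure artefact would also appear maintained.
4. If a second pre-treatment ACQ that did not decide eligibility was collected for all patients, use it as baseline. This removes the regression to the mean in the model above, though not the effect of education or time. Do not change the baseline definition for the last patients only: 52 of 56 had been recruited by October 2025, and two definitions would then be mixed in one analysis.

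The cost is wording, with no extra patients or visits. The downside is a narrower claim: how the two interventions compare, without a stand-alone effect of either. Results are expected by the end of December 2026, so the wording can still be settled before they are reported.

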### Strengths and Limitations of the Study

This study protocol will be a randomized trial with a 4-month follow-up postintervention. It is essential to determine whether the possible gains will be maintained in the medium term following the intervention. Objective measures of physical activity and sleep quality (ActiGraph GT9X), physical fitness (CPET), and body composition (Octopolar InBody 720) are another strength of this study. One limitation is that assessments using questionnaires are considered subjective measures. However, all tools have been validated and are widely used in interventions for people with asthma. The fact that the study will be conducted in a single hospital center may represent another limitation.

### Conclusions

To the best of our knowledge, this will be the first study to compare the effects of AT versus BI on increasing physical activity for clinical asthma control. Therefore, the results obtained in the proposed protocol may provide essential information for health care professionals when recommending these approaches to people with asthma. Additionally, this study may help clarify whether the potential short-term gains following the intervention are maintained in the medium term in people with moderate to severe asthma.

## Appendix

Multimedia Appendix 1 Peer-review report by FAPESP (São Paulo Research Foundation, Brazil).

## Abbreviations

ACQ: Asthma Control Questionnaire
AT: aerobic training
BI: behavioral interventions
CPET: cardiopulmonary exercise testing
HR: heart rate
PADL: physical activity in daily life
RCP: respiratory compensation point
SPIRIT: Standard Protocol Items: Recommendations for Interventional Trials
SpO2: peripheral oxygen saturation
VCO2: carbon dioxide production
VO2: oxygen consumption
